### Statistical methods

Continuous general characteristics and laboratory test variants will be described by medians when they do not conform to the Kolmogorov–Smirnov test and by means when do. The Chi-square test will be used to evaluate independent binomial variables. All hypothesis tests are two-sided except for the primary outcome and a p value < 0.05 is considered of significance. For the primary outcome, the paired results of the ddPCR assay and BC will be analyzed using McNemar's test. Wilcoxon rank-sum test will be used to compare efficacy grades, Fisher's exact test to compare effective rates, and CMH (Cochran-Mantel–Haenszel) method to compare the efficacy grade and response rate after deducting the central effect. Multivariate analysis of multivariate mixed effects logistic regression can be used for outcome variables, and multivariate analysis of variance-adjusted Cox models can be used for time-event outcome variables. Apart from multivariate analysis, and propensity score methods may be used to control bias. In this trial, there will be an intention-to-treat (ITT) analysis as randomized analysis, including that of discontinuation and deviation. Also, sensitivity analysis will be used to ensure appropriate interpretation. Methods like multiple imputation will be used to handle missing data. Figures and statistical analyses will be conducted using the Prism 9.0 software (GraphPad Software, San Diego, CA, the USA), SPSS Version 20.0 (IBM Corp., Armonk, NY, USA), and R studio 4.0.3 software (R studio Software, Boston, MA, USA).

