### Diagnostic methods

The ddPCR assay can identify over fifteen pathogens, covering the most common bacteria and fungi in BSIs according to the China Antimicrobial Surveillance Network 2021 Report (CHINET, http://www.chinets.com) [19] and seven antibiotic resistance genes. Droplet digital PCR analysis was performed using a 5-fluorescent-channel droplet digital PCR system (Pilot Gene Technology (Hangzhou) Co., Ltd.).

When evaluating the diagnostic test accuracy of ddPCR method, positive and negative results compared with the reference method (a synchronous blood culture) are defined according to a previous study [20]. The four possible results of the paired tests are in the following: Positive consistency (true positive, TP): In addition to the complete consistency between ddPCR results and the synchronous blood culture results, it also includes three situations: ddPCR results include additional pathogens, ddPCR test and simultaneous blood culture have results in common and both have independent detection of pathogens, ddPCR results are included in the simultaneous blood culture results; Negative inconsistency (false positive, FP): When the synchronized blood culture is negative, the ddPCR assay independently detects pathogens; Positive inconsistency (false negative, FN): When the ddPCR test is negative, the pathogens are independently detected by the synchronous blood culture. Or pathogens are independently detected by the ddPCR test and the synchronous blood culture without overlapping; Negative consistency (true negative, TN): No pathogen is detected by the ddPCR test nor the synchronous blood culture.

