### Sample size calculation

The predicted sample size is calculated to achieve the primary outcome, which is evaluating the diagnostic test accuracy of the ddPCR method (our index test) compared with the reference test.

According to previous published studies evaluating diagnostic accuracy of ddPCR in patients with suspected sepsis, expected test sensitivity (SN) and specificity compared with blood culture are 85% and 75%, respectively according to our pre-test and the previous studies [11, 14]. And the estimated disease prevalence (P), which is the blood culture positive rate in this case, is around 3% to 15% [5, 21, 22]. Therefore, based on the sample size calculation statistical methodology incorporating in the prevalence of disease [23, 24], with a significance ($$\alpha$$) level of 0.05, a 95%CI width of 10% and a prevalence of 3%, the sample size for the experimental group is:$$\mathrm{N}1=\frac{TN+FN}{P}= {Z}\alpha^2/2\frac{SN(1-SN)}{{W}^{2}*P}=1632.$$

Since patients will be allocated into two groups with a ratio of 3:1, the total sample size of the two groups combined is 1632/3*4 = 2176. Assuming a 5% drop-out rate in follow-up, the sample size is calculated to be 2292 patients.

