### Outcome measures

The primary outcome of this trial is the diagnostic efficacy of the ddPCR assay (the index test). The estimated sensitivity and specificity will be determined by comparing ddPCR assay results with the synchronous blood culture (the reference test) results from the prospective clinical specimens. Secondary outcomes between two arms consist of clinical outcomes and surrogate endpoints and fall into four categories: ① Clinical indicators: mortality rates at follow-up time points until day 90, the mean Sequential Organ Failure Assessment (SOFA) score at follow-up time points, the length of stay in the hospital or in the ICU, time to remission from shock (if there is septic shock), duration of mechanical ventilation or vasoactive drug application, rates of new requirement for renal replacement therapy;② Microbial and antibiotic usage indicators: time from enrollment to identification of a pathogen or the directed antimicrobial therapy, duration of major broad-spectrum antibiotics(glycopeptide, carbapenem) use, duration of antibiotic use;③ Quality of life indicator: the EQ-5D-5L score on day 90, which is a standardized measure of health-related quality of life developed by the EuroQol Group comprising five dimensions: mobility, self-care, usual activities, pain and discomfort, and anxiety and depression.④ Health economic indicators: total cost during hospital stay.

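### The only analysis named for the primary outcome is a McNemar test outside the two-sided rule; it compares how often ddPCR and blood culture are positive and tests neither sensitivity nor specificity

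*Protocol article*

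**What the plan says.** Outcome measures defines the primary outcome as diagnostic efficacy: "The estimated sensitivity and specificity will be determined by comparing ddPCR assay results with the synchronous blood culture (the reference test) results".

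Sample size calculation treats this as an estimation problem. It assumes that "expected test sensitivity (SN) and specificity compared with blood culture are 85% and 75%, respectively", puts the culture-positive rate at a value that "is around 3% to 15" per cent, and sizes the ddPCR arm at 1632 with "a 95%CI width of 10% and a prevalence of 3" per cent. The formula uses the two-sided normal quantile. The section gives no null value, power or minimum acceptable accuracy.

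Statistical methods then assigns a hypothesis test: "For the primary outcome, the paired results of the ddPCR assay and BC will be analyzed using McNemar's test". The sentence before it reads: "All hypothesis tests are two-sided except for the primary outcome and a p value < 0.05 is considered of significance". The primary test is thus one-sided by exception; its direction is not given.

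Diagnostic methods defines the four cells of the ddPCR/culture table. The false-negative cell holds culture-positive patients with a negative ddPCR result, and also some patients positive on both: "Or pathogens are independently detected by the ddPCR test and the synchronous blood culture without overlapping".

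**The concern.** In a table of ddPCR against culture, McNemar's test uses only the two discordant cells: ddPCR positive with culture negative, and ddPCR negative with culture positive. Its null hypothesis is that the two methods are positive equally often.

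Sensitivity is TP/(TP+FN) and specificity is TN/(TN+FP). Neither TP nor TN enters the McNemar statistic, so the test cannot address either quantity. McNemar's test is suitable for comparing two index tests against a third reference. Here culture is itself the reference, so its own sensitivity and specificity are 100% by definition and there is no second accuracy to compare.

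The direction of the evidence is also awkward. With few culture positives and an expected specificity of 75%, false positives dominate the discordant pairs, and each additional one lowers the p value for ddPCR being positive more often. At stake is the one inferential statement attached to the primary outcome: a p value that cannot tell an accurate assay from an uninformative one with the same specificity. It also does not match the sample size, which rests on the two-sided precision of sensitivity.

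**Working it through.** **Inputs.** From Sample size calculation: N = 1632 in the ddPCR arm, culture-positive rate P = 3% (range up to 15%), sensitivity SN = 85%, specificity SP = 75%, W = 10%. From Statistical methods: one-sided test at 0.05. Assumptions: one pair per patient, plain positive/negative results, and the direction ddPCR positive more often than culture, since none is stated.

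**The plan's own figure.** N1 = z² × SN(1−SN)/(W² × P) = 1.96² × 0.85 × 0.15/(0.10² × 0.03) = 1632.6, against 1632 stated. Then 1632 × 4/3 = 2176. Carrying 1632.6 through, 2176.8/0.95 = 2291.4, which rounds up to 2292. The figures reproduce, with W acting as the half-width of a two-sided interval for sensitivity.

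**McNemar's test at these figures.** Expected counts are FP = N(1−P)(1−SP) and FN = N × P × (1−SN), with z = (FP−FN)/√(FP+FN).

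For the planned assay at 3%: FP = 1632 × 0.97 × 0.25 = 395.8; FN = 1632 × 0.03 × 0.15 = 7.3; z = 388.4/√403.1 = 19.35.

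For an assay positive at random in 25% of patients (sensitivity 25%, specificity 75%): FP is the same; FN = 1632 × 0.03 × 0.75 = 36.7; z = 359.0/√432.5 = 17.26.

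| Assay (SN/SP) | P | FP | FN | z | one-sided p |
|---|---|---|---|---|---|
| Planned, 85/75 | 3% | 395.8 | 7.3 | 19.35 | 1e-83 |
| Random 25% positive, 25/75 | 3% | 395.8 | 36.7 | 17.26 | 4e-67 |
| No culture positive found, 0/75 | 3% | 395.8 | 49.0 | 16.45 | 5e-61 |
| Planned, 85/75 | 15% | 346.8 | 36.7 | 15.83 | 9e-57 |
| Random 25% positive, 25/75 | 15% | 346.8 | 183.6 | 7.09 | 7e-13 |

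In 20,000 simulated tables per scenario with the exact one-sided test, both the planned and the random 25% assay were significant in about 100% of tables at either prevalence.

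**The other end.** A perfect assay has FP = FN = 0, hence no discordant pairs, and cannot be significant in either direction. With FN = 0, the exact one-sided p is 0.5 to the power FP: 0.0625 for four false positives and 0.031 for five. Five are needed, so an assay with no false negatives and observed specificity above about 1 − 5/1583 = 99.7% is not significant.

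**Where the pattern does not hold.** At P = 3%, a random assay whose positive rate equals P is significant in about 4% of simulated tables. At P = 15%, a random assay positive in 10% has z = −4.31, so it is not significant in this direction. A 99/99 assay is significant in 99.5% of tables at P = 3% and 87% at P = 15%.

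**What the intervals would show.** With about 49 culture positives, 42 of 49 detected gives an exact 95% interval for sensitivity of 72.8% to 94.1%; 12 of 49 gives 13.3% to 38.9%. The planned and the random assay, almost alike under McNemar's test, are clearly separated.

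**The case against.** **The estimates are planned anyway.** This stands. Outcome measures says sensitivity and specificity will be estimated, and Diagnostic methods defines the cells for it. A reader might infer that the primary question goes unanswered; the document does not support that. The fault lies in the test attached to the estimates.

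**No passage makes p < 0.05 the success criterion.** This stands too. A reader might infer that any useless assay would pass and any near-perfect one would fail. There is no pass rule, and the counter-examples in the working show that the behaviour depends on the assay's positive rate relative to culture. The defect is that significance is unrelated to accuracy, not that it is always reversed.

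**McNemar's test has a sensible use here.** The Background lists consistency with conventional culture among the aims and calls culture sensitivity relatively low. Whether ddPCR is positive more often than culture is a coherent paired question. That supports keeping the test as a secondary comparison, not as the analysis of sensitivity and specificity.

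**The false-negative cell.** Counting patients positive on both tests without a shared organism as false negatives would spoil the McNemar comparison if those cells were used. Statistical methods refers only to the paired results, and plain positive/negative pairing fits that equally well. A mismatch is possible but not established.

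**Detail belongs in the analysis plan.** The interval method, and perhaps the direction and null, may be set there. The choice of test, however, is made in the article and does not suit the stated outcome.

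**Conclusion.** The concern holds in this limited form and should be corrected. The only analysis that Statistical methods names for the primary outcome tests neither of its two components and does not match the interval-based sample size. At the expected 75% specificity, false positives settle significance in advance: z is 19.35 for the planned assay and 17.26 for a random one at 3% prevalence, and the random assay still reaches 7.09 at 15%.

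These figures rest on expected counts at the plan's own assumptions, plain positive/negative pairing, and the direction ddPCR above culture. The central conclusion does not depend on direction: an always-positive assay is significant one way, an always-negative one the other way, and a perfect assay neither way.

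**What to change.** In Statistical methods:

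- State that the primary analysis is the estimated sensitivity and specificity from the day-0 ddPCR/blood culture pair, each with a two-sided 95% confidence interval, in line with the sample size calculation.
- Remove the exception for the primary outcome from the two-sided rule.
- Either drop McNemar's test, or keep it as a two-sided secondary comparison of positivity rates on plain positive/negative pairs, described as such and not as evidence of diagnostic accuracy.

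The cost is a change of wording. No new data are needed and the sample size is unchanged, because it already rests on a two-sided interval for sensitivity.

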### Randomization

After being enrolled in the trial, participants will be assigned randomly to either the ddPCR group or the control group using the stratified block randomization method. Stratification is designed to balance the two arms for age (< 65 years or ≥ 65 years) and setting (10 medical centers), the two factors that may jeopardize study conclusions. An online random system is built by a third-party company. The system is used to generate and save the random lists by giving separate blocks for each of the twenty combinations in advance. The block width is an integer multiple of 4 since the ratio is 3:1. In order to prevent manipulation of group assignment during recruitment, the specific block size will be disclosed at the end of this trial by the third-party company to the Huashan PROGRESS project team, who generates the allocation sequence after enrollment. Patients will be recruited consecutively and it is competitive enrollment among the medical centers.

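### Randomisation is stratified by age and centre, but the committed between-arm tests use no strata or centre only, and three of them are tied to outcomes the protocol does not define

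*Protocol article*

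**What the plan says.** Protocol article, Randomization: "Stratification is designed to balance the two arms for age" (cut at 65 years) and "setting (10 medical centers), the two factors that may jeopardize study conclusions". The random lists are made by "giving separate blocks for each of the twenty combinations in advance", and "The block width is an integer multiple of 4 since the ratio is 3:1".

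Protocol article, Statistical methods, commits to four between-arm tests:
- "The Chi-square test will be used to evaluate independent binomial variables", with no outcome named.
- "Wilcoxon rank-sum test will be used to compare efficacy grades".
- Fisher's exact test, for effective rates.
- CMH, as a "method to compare the efficacy grade and response rate after deducting the central effect".

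The same section then permits, without requiring, mixed-effects logistic regression for outcome variables and adjusted Cox models for time-to-event variables. It names no covariates for either. It adds: "Apart from multivariate analysis, and propensity score methods may be used to control bias".

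Protocol article, Outcome measures, lists the between-arm outcomes: mortality to day 90, mean SOFA, hospital or ICU stay, time to shock remission, duration of ventilation or vasoactive drugs, new renal replacement therapy, time to pathogen identification or directed therapy, antibiotic durations, EQ-5D-5L at day 90 and total hospital cost.

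**The concern.** Two mismatches meet in one paragraph of the protocol.

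First, the design singles out age and centre as the factors that could threaten the conclusions and restricts the randomisation on both. The one committed test that uses strata removes centre only, and the other three use none. An analysis that ignores strata on which the randomisation was balanced overstates the variance of the treatment difference and loses power.

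Second, three of the four committed tests are assigned to endpoints that the trial does not measure. For mean SOFA, EQ-5D-5L and cost, no comparison is named that clearly fits: the opening sentence on means and medians is descriptive, and the model permitted for outcome variables is logistic.

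At stake are the secondary comparisons between arms. They matter because the Discussion presents the effect of ddPCR on clinical outcomes as the reason for randomising, and because the 3:1 ratio leaves a control arm of 2292 / 4 = 573.

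**Working it through.** **The plan's own figure.** Sample size calculation gives 1632 for the ddPCR arm, 2176 in total and 2292 after 5% drop-out. With sensitivity 0.85, prevalence 0.03 and 10% entered as the half-width, 1.96² × 0.85 × 0.15 / (0.10² × 0.03) = 1632.6. Then 1632 × 4/3 = 2176, and 2176 / 0.95 gives 2291; rounding the ddPCR arm up to 1719 gives 1719 × 4/3 = 2292. The figure reproduces to within rounding. It serves the accuracy outcome and does not depend on the point raised here.

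**Tests set against outcomes.**

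| Named method | Status | Strata | Assigned to | Matching defined outcome |
|---|---|---|---|---|
| Chi-square | committed | none | binomial variables | mortality, new renal replacement |
| Wilcoxon | committed | none | efficacy grades | none |
| Fisher | committed | none | effective rates | none |
| CMH | committed | centre | efficacy grade, response rate | none |
| Mixed logistic | permitted | not stated | outcome variables | mortality, new renal replacement |
| Cox | permitted | not stated | time-to-event variables | time outcomes |

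**What ignoring the strata costs, for a binary outcome.** Inputs from the protocol: N = 2292, 3:1 allocation, 20 strata (2 age groups × 10 centres), two-sided 0.05. Assumptions:
- blocks of 4;
- strata of equal expected size and no drop-out;
- event risk near 25%, the midpoint of the Background's mortality range, (1/6 + 1/3)/2;
- treatment odds ratio 0.73;
- the centre and age effects shown in the table below.

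The statistic over strata k is

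z = Σ(x_Tk − n_Tk·m_k/n_k) / √Σ[n_Tk·n_Ck·m_k(n_k − m_k) / (n_k²(n_k − 1))],

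where x_Tk is the number of events in the ddPCR arm, m_k all events, n_Tk and n_Ck the arm sizes, and n_k their sum. It is computed with 1 stratum (in effect the unstratified chi-square), 10 strata (centre) and 20 strata (centre by age). There were 20,000 null runs and 10,000 alternative runs per scenario. Each cell gives type I error / power, in percent.

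| Centre log-odds SD, age odds ratio | Unstratified | Centre CMH | Centre-by-age CMH |
|---|---|---|---|
| 0, 1 | 4.7 / 78.25 | 4.7 / 78.28 | 4.7 / 78.28 |
| 0.3, 1.5 | 4.7 / 76.62 | 4.9 / 77.10 | 5.0 / 77.26 |
| 0.6, 2 | 4.1 / 73.38 | 4.8 / 75.44 | 5.0 / 76.03 |
| 1.0, 3 | 3.0 / 64.62 | 4.4 / 71.89 | 5.1 / 73.54 |

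Power lost against centre-by-age CMH, for the last three rows:
- Unstratified: 77.26 − 76.62 = 0.64; 76.03 − 73.38 = 2.65; 73.54 − 64.62 = 8.92 points.
- Centre only: 77.26 − 77.10 = 0.16; 76.03 − 75.44 = 0.59; 73.54 − 71.89 = 1.65 points.

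Monte Carlo standard error is about √(0.05 × 0.95 / 20,000) = 0.15 points for type I error and √(0.75 × 0.25 / 10,000) = 0.43 points for a single power. The three tests were run on the same simulated trials, so their differences are more precise than that.

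The direction is as theory predicts. Balance within strata removes between-stratum variation from the true variance of the comparison, while the unstratified formula still counts it.

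**The case against.** The strongest reply is that this is a condensed article. The permitted mixed logistic and Cox models can carry age and centre, the covariate list belongs in an analysis plan that is not shown, and the section promises an intention-to-treat analysis. This stands in part. A reader might infer that age is excluded from the analysis; the text supports no more than that the CMH description names centre alone and that Statistical methods does not mention age. The reply does not cover the committed tests, whose strata and endpoints the article itself fixes.

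A reader might also infer that the secondary outcomes have no usable test. That is too broad: chi-square fits mortality and new renal replacement, and Cox fits the time outcomes. The mismatch with Outcome measures is confined to Wilcoxon, Fisher and CMH.

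A third inference is that false-positive findings become more likely. The simulation shows the reverse, and the losses are small unless the stratum effects are strong.

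On propensity scores, it is tempting to say they have no place because allocation is fixed at 3:1. Randomisation does remove systematic confounding, but weighting by an estimated propensity is a recognised form of covariate adjustment, and the protocol offers it only as an addition. Whether the choice would be made with open-label results in view cannot be known without the analysis plan. What stands is that it should not be the main randomised comparison.

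**Conclusion.** The point holds as a wording defect in the secondary between-arm analyses. The committed tests do not follow the stratified design, and three of the four are attached to undefined endpoints. The paired primary outcome is untouched, and the protocol claims no power for the secondary outcomes.

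For a binary outcome near 25%, following the unstratified test as written costs roughly 1 to 9 points of power as assumed stratum effects go from weak to strong. Leaving age out of the centre CMH accounts for at most about 2 points. These sizes rest on assumed centre and age effects, equal strata and full follow-up; the documents give no values for the stratum effects. Time-to-event and continuous outcomes were not simulated.

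Adjusting for day-0 SOFA is a recommended gain, and its absence from the article is not an error. A reader might turn an assumed correlation into an equivalent number of extra patients. The documents do not support that: they state no correlation, and the Discussion says follow-up apart from the day-90 call takes place in hospital, so later SOFA is missing after death or discharge.

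**What to change.** In Statistical methods, delete the references to efficacy grades, effective rates and response rate, and name the outcomes listed under Outcome measures. Then fix one main between-arm analysis per outcome type, as randomised, with age stratum and centre included:
- Mortality and new renal replacement: mixed-effects logistic regression.
- Time outcomes: Cox model stratified by centre and age stratum, with death treated as a competing event where relevant.
- SOFA, EQ-5D-5L and cost: linear mixed model.

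Add day-0 SOFA as a covariate for SOFA and mortality, without claiming a sample-size equivalent. Keep the unstratified tests and any propensity-score analysis as labelled sensitivity analyses.

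The cost is wording only: no new data and no change in sample size. Age and centre are already recorded for randomisation. Day-0 SOFA is assumed to be computable from the examinations listed under Duration of follow-up.
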